## Abstract

**Introduction::**

Hypertension can lead to different degrees complications of cardiovascular and cerebrovascular, and increase the risk of sudden death. Acupuncture has become a complementary alternative therapy for hypertension because of its antihypertensive and nontoxic side effects. However, there is still lack of evidence-based medicine evidence for an effective acupuncture antihypertensive prescription. The purpose of this study is to evaluate the effect of a special acupuncture prescription on hypertension with hyperactivity of liver yang.

**Methods::**

In this randomized controlled trial, we will recruit 56 hypertensive patients with hyperactivity of liver yang. Then the patients will be randomly divided into control group and experimental group. The control group will be treated with western medicine, and the experimental group will be treated with medicine combined with acupuncture. The intervention will last 4 weeks. The indices will be collected before acupuncture, after acupuncture, and 2 weeks after acupuncture. The primary outcome will be 24-hour ambulatory blood pressure. The secondary outcomes will be clinic blood pressure, anxiety and depression score, and the syndrome score of hyperactivity of liver yang. The auxiliary indicators will be blood pressure load values and salt sensitivity risk rate. The exploratory indicator will be acupoint diagnosis. The safety evaluation indicator will be incidence of adverse events.

**Discussion::**

The results of this study will provide favorable evidence for the efficacy and safety of acupuncture in reducing blood pressure, and explore the positive reaction acupoints which related to hypertension.

## Introduction

1

Hypertension is one of the chronic diseases that seriously endanger human health. A study on hypertension epidemiology in 90 countries shows that the awareness rate of hypertension in adults is only 46.5%, the treatment rate is 6.9%, and the proportion of good blood pressure control is only 13.5%.^[1]^ The prevention and treatment of hypertension is still haunting the world. Most of the time, the treatment of hypertension is lifelong medication. The long-term use of antihypertensive drugs will bring damage of gastrointestinal, liver, and kidney function. In addition, antihypertensive drugs have the disadvantages of poor compliance and high cost of lifelong medication. Therefore, in recent years, in many countries’ hypertension treatment guidelines, it is mentioned to strengthen the intervention of non-drug therapy. In the review and analysis of clinical research report on acupuncture published by the World Health Organization,^[2]^ essential hypertension is definitely recommended as a disease for acupuncture treatment. This is obviously a confirmation of the antihypertensive effect of acupuncture. Acupuncture, as a characteristic therapy of traditional Chinese medicine (TCM), has the advantages of green and safety, and can adjust the body in multiple levels. With the international development of acupuncture, it has great potential and space in the prevention and treatment of global hypertension.

The synergism and attenuation effects of acupuncture on hypertension is a research hotspot at present. Whether it can produce better therapeutic effect on hypertension is the focus of our research. Some literatures have compared the clinical trials of different acupuncture prescriptions in the treatment of hypertension, and found that the antihypertensive effect of acupuncture combined with medicine is better than that of Western medicine alone. And the acupuncture prescription following the principle of dialectical treatment has obvious antihypertensive effect, otherwise, the effect are not good.^[3]^ Therefore, it is necessary to find a suitable prescription for acupuncture to reduce blood pressure, and strengthen the synergism and attenuation effects of acupuncture by combining with western medicine.

The purpose of this study is to evaluate the efficacy and safety of a special acupuncture prescription on hypertension with hyperactivity of liver yang (HLY), and to explore the positive reaction acupoints of patients with hypertension.

## Method

2

### Experimental design

2.1

This is a single-center, single-blind, randomized, controlled, parallel group clinical trial. The selected patients will be divided into control group and experimental group according to the ratio of 1:1. The latter will receive acupuncture treatment for 4 weeks on the basis of the former. The data will be collected before acupuncture, after acupuncture, and 2 weeks after acupuncture. The process is shown in Figure 1.

**Figure 1 F1:**
[figure not shown]
Flow chart of the study design.

## Participants

3

### Source of participants

3.1

The participants in this study will be recruited from Dongzhimen Hospital of Beijing University of Chinese Medicine and its surrounding communities.

### Diagnostic criteria

3.2

#### Diagnostic criteria of western medicine

3.2.1

The diagnosis criteria of essential hypertension will be in accordance with the 2018 revision of the guidelines for prevention and treatment of hypertension of China, revised by the China hypertension Revision Commission.^[4]^ Without antihypertensive drugs, hypertension will diagnosed when systolic blood pressure (SBP) of clinic blood pressure (CBP) ≥140 mmHg and/or diastolic blood pressure (DBP) of CBP ≥90 mmHg are measured 3 times (not on the same day). The patients who had the history of hypertension and were taking antihypertensive drugs will also be diagnosed with hypertension. The diagnostic criteria of ambulatory blood pressure monitoring (ABPM) for hypertension are: 24 hour average SBP/DBP ≥130/80 mmHg; daytime SBP/DBP ≥135/85 mmHg; nighttime SBP/DBP ≥120/70 mmHg. The diagnostic criteria of home blood pressure monitoring (HBPM) ≥135/85 mmHg, which corresponded to 140/90 mmHg in CBP.

According to whether participants has cardiovascular risk, including target organ damage, cardiovascular risk factors, diabetes, and clinical complications, they will divided into 4 levels: low risk (without risk factors), medium risk (with 1–2 risk factors), high risk (with ≥3 risk factors), very high risk (with target organ damage, chronic kidney disease stage 3, or diabetes).

#### TCM diagnostic criteria

3.2.2

According to the expert consensus on diagnosis and treatment of hypertension in TCM (2019 edition),^[5]^ the guiding principles for clinical research of new Chinese medicine in the treatment of hypertension^[6]^ and the criteria for diagnosis and treatment of TCM syndromes (2017 edition),^[7]^ the TCM diagnostic criteria for HLY will be formulated. On the basis of the main symptoms, those who have ≥3 secondary symptoms at the same time combined with tongue and pulse conditions, can be diagnosed as HLY.

To guarantee the consensus on inquiry method, judgment of syndrome type and record method, the clinical data will be collected by unified questionnaire and unified criteria. It will be reviewed by the deputy chief physician and above. If the judgment of syndrome type is inconsistent, 2 chief physicians of TCM will assist in the diagnosis.

### Inclusion criteria

3.3

1.Age: 18 to 65 years, both male and female;2.Met the Western diagnostic criteria of essential hypertension. For patients without antihypertensive drugs, SBP: 140 to 179 mmHg and/or DBP: 90 to 109 mmHg. For patients with antihypertensive drugs, hypertension should be stabilized at a normal high value. The patients who took medicine used ≤2 antihypertensive drugs for >2 months.3.Confirmed TCM diagnosis of HLY in hypertension.4.Not receives acupuncture or Chinese herbal medicine treatment in recent 1 month.5.Good compliance with the observation and evaluation of researchers.6.Informed consent is signed by the patient himself or his immediate family members.

### Exclusion criteria

3.4

1.Secondary hypertension, such as aldosteronism, pheochromocytoma, Cushing syndrome, gestational hypertension, obstructive sleep apnea hypopnea syndrome, and so on.2.Accompanied by other serious cardiovascular and cerebrovascular diseases, nephropathy, retinopathy, peripheral vascular diseases, diabetes, blood diseases, and so on.3.There were skin diseases and severe skin damage near the acupoints.4.Mental disorders, pregnant, and lactating women.5.Participating in other clinical trials.

### Elimination of participants and their treatment

3.5

#### Elimination criteria

3.5.1

1.The patients who do not complete the treatment according to the regulations or the data are incomplete, which affect the later evaluation.2.Noncompliant patients, those who withdraw from the research by themselves.3.Unauthorized use of drugs and treatment methods other than those specified in this protocol.4.During the trial, patients with serious adverse reactions or complications. The patients are intolerant of acupuncture therapy, or should not continue to receive treatment.5.Patients lost to follow-up.

#### Treatment of elimination participants

3.5.2

1.When the patients falls off, we will contact by telephone, e-mail, and so on, as far as possible to ask for the reason. Record the time of the last treatment and complete the assessment items that can be completed.2.Patients who withdraw from the trial due to adverse reactions or ineffective treatment will take corresponding measures according to their actual situation.3.Intention analysis will be conducted after the end of the trial, then the reason and time of withdrawal will be recorded in detail. Those who had more than half course of treatment will be included in the statistical analysis of curative effect.

### Termination criteria

3.6

1.Patients with serious adverse reactions, special physiological changes, and other unexpected events during the study period.2.Patients with severe complications, disease progression, and other critical illness during the study period.3.Patients who did not obey the treatment.

## Research methods

4

### Random scheme and random hiding

4.1

This study will adopt a single-center, randomized, single blind, simple positive drug control method. Simple random number method will be used for grouping. Input the expected sample size into the statistical software package PEMS3.1, and get the sequence number. Then make a random card and add an opaque envelope to seal it. When the qualified patients enter the trial, the envelopes will be opened according to the order of entry, and they will be grouped according to the information on the random card.

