### Estimation of sample size

4.2

The purpose of this study is to observe that the antihypertensive effect of acupuncture combined with medicine is not inferior to that of Western medicine alone. Therefore, the sample calculation is based on the sample content calculation formula of noninferiority test.^[8]^ The calculation result is 22.57, that is, the experimental group and the control group need about 23 patients, respectively. According to the shedding rate of 20%, a total of 56 patients will be recruited.

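### Simple, unstratified allocation of 56 patients leaves balance on antihypertensive drug use at entry to chance, and the analysis section names no adjustment for it

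*Protocol article*

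**What the plan says.** All references are to the protocol article.

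- Section 4.1 (Random scheme and random hiding) gives the allocation rule: "Simple random number method will be used for grouping". On how the list is made it says: "Input the expected sample size into the statistical software package PEMS3.1, and get the sequence number". Sealed opaque envelopes are then opened in order of entry. No block, stratum, minimisation or fixed arm total is mentioned.
- Section 2.1 (Experimental design) has patients "divided into control group and experimental group according to the ratio of 1:1".
- Section 4.2 (Estimation of sample size) says that "the experimental group and the control group need about 23 patients, respectively", and then: "According to the shedding rate of 20%, a total of 56 patients will be recruited".
- Section 3.3 (Inclusion criteria) sets separate entry rules by drug use. Untreated patients need SBP 140-179 and/or DBP 90-109 mmHg. For the others: "For patients with antihypertensive drugs, hypertension should be stabilized at a normal high value". No figure is attached to that level.
- Section 6.1 makes 24-hour ambulatory blood pressure the main outcome, measured in weeks 1 (baseline), 5 and 7.
- Section 9 (Statistical analysis) plans repeated-measures analysis of variance for blood pressure and t tests for measurement data in general. It names neither drug use nor baseline blood pressure as an adjustment term.

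**The concern.** Drug use at entry is recorded for everyone, is known before allocation, and determines which blood pressure range a patient must meet to enter. That makes it the obvious factor to balance in a 56-patient trial with blood pressure as the outcome. The allocation method does not balance it, and the stated analysis does not account for it.

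Drug status may also bear on the change in blood pressure. Under sections 5.1 and 5.2 both arms receive western medicine, and controls continue their original treatment unchanged. A patient who enters untreated has no original treatment to continue, and the article does not say what that patient then receives. If untreated and treated entrants follow different courses over the four weeks, an arm with more of one kind would show a different mean change whatever acupuncture does.

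At stake are precision and the ease of reading one small trial. The validity of the test is not at stake. The list has to be settled before the first envelope is opened; the model terms can be fixed later, but should be fixed before the data are seen.

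**Working it through.** **Inputs.** From the article: 56 patients, 1:1, 23 evaluable per arm (22.57 before rounding), 20% loss, simple random numbers. Not in the article, so assumed: the share of patients on drugs (30%, 50% or 70%, that is 17, 28 or 39 of 56) and any blood pressure gap between treated and untreated entrants.

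**1. The plan's own total.** 23 × 1.2 = 27.6, so 28 per arm and 56 in total. Dividing by the retention rate gives 2 × 22.57 / 0.8 = 56.4 unrounded, or 23 / 0.8 = 28.75, so 29 per arm and 58. The stated 56 is therefore reproduced by the first form and is within 2 patients of the second. The 22.57 cannot be reproduced because its inputs are not shown; nothing below depends on it.

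**2. Arm sizes, if each patient is allocated independently.** One arm's size is Binomial(56, 0.5).

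| Split | Probability | Information relative to 28:28 (4·n₁·n₂ / 56²) |
|---|---|---|
| exactly 28:28 | 10.6% | 100% |
| 24:32 or worse | 35.0% | 98% at 24:32 |
| 22:34 or worse | 14.1% | 4 × 22 × 34 / 3136 = 95% at 22:34 |
| 20:36 or worse | 4.4% | 4 × 20 × 36 / 3136 = 92% at 20:36 |

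**3. Imbalance in drug use.** Let K patients be on drugs, a of them in the first arm, with arm sizes n₁ and n₂. The difference in shares is a/n₁ − (K − a)/n₂. Under simple allocation, a is Binomial(K, 0.5) and the number of untreated patients in that arm is an independent Binomial(56 − K, 0.5). Under a fixed 28:28 list, a is hypergeometric.

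| Share on drugs (assumed) | K | P(difference ≥ 20 points), simple | Same, unstratified 28:28 |
|---|---|---|---|
| 30% | 17 | 11.9% | 8.0% |
| 50% | 28 | 14.1% | 18.1% |
| 70% | 39 | 11.9% | 8.0% |

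The 28:28 column jumps because differences move in steps of 2/28 = 7.1 points. At K = 28 the first value above 20 is 6/28 = 21.4 points; at K = 17 or 39 it is 7/28 = 25.0 points. At more extreme shares the probabilities fall: on a 28:28 list, to about 4% at a 20% share and 2% at a 10% share.

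**4. What a 20-point imbalance does.** It moves the difference between arm means by 0.20 × the gap between treated and untreated entrants. For an assumed gap of 10-25 mmHg in baseline SBP that is 0.20 × 10 = 2 to 0.20 × 25 = 5 mmHg. This is a shift in baseline means. The estimated effect on change moves by one fifth of whatever difference in change exists between the two kinds of patient, a quantity the article gives no basis for.

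**5. Cost of adjusting.** With equal arms and half the patients on drugs, the correlation between arm and drug use equals the difference in shares. The variance inflation is 1 / (1 − 0.20²) = 1.04, or about 4%.

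**6. After stratifying.** With permuted blocks of 4 within each drug-use stratum (5,000 simulated trials at each assumed share), the largest difference in arm size was 2 patients, the largest difference in drug-use share was 3.6 points, and no trial reached 20 points. A block of 6 can leave an excess of 3 in a stratum. With 17 on drugs and opposite excesses in the two strata, the shares are 10/28 against 7/28, or 10.7 points apart, still well short of 20.

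**The case against.** The strongest reply is that simple randomisation is valid. Chance imbalance neither biases the comparison nor raises the type I error. That is correct and limits the point to precision and interpretability.

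Second, a reader might infer that a baseline shift passes straight into the treatment estimate through unadjusted t tests. Section 9 does not support that: it assigns blood pressure to repeated-measures analysis of variance, and baseline is one of the three visits. A constant difference between arms does not enter the group-by-time comparison. Only a difference in change by drug status would carry over.

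Third, a reader might infer that the trial is likely to miss its 23 per arm because of the allocation method. With independent 20% loss, the chance that both arms keep 23 is 11.9% under simple allocation, but only 25.1% even at 28:28. Most of that shortfall comes from 28 × 0.8 = 22.4 already lying below 23. The arm-size issue disappears altogether if entering the total into the software produces a list with 28 in each arm, which the stated ratio and equal arm sizes would fit. The article does not say either way. The drug-use issue remains with such a list.

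Fourth, the two entry groups might be read as sharply separate in systolic pressure. Untreated patients can enter on diastolic pressure alone, and the high-normal level has no number, so no systolic gap can be derived from the entry limits.

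Finally, blocks make allocation somewhat easier to guess where, under section 4.3, only evaluators and statisticians are blinded. This is a genuine cost.

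**Conclusion.** The point holds as a modest, inexpensive improvement. Nothing in the stated allocation or analysis deals with drug use at entry, although the entry criteria tie it to blood pressure. The probability of a 20-point or larger imbalance is about 12-14% under simple allocation and 8-18% under an unstratified 28:28 list, assuming that 30-70% of patients take drugs; it is lower at more extreme shares. The consequence is some loss of precision and a result that is harder to interpret, chiefly if drug status also predicts the change in blood pressure, which the article leaves open. Unequal arms on their own are a minor matter, and only if the list is not fixed at 28:28. The documents do not support a claim of bias or of an invalid test.

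**What to change.** Before the first patient, replace the simple list with a 1:1 list stratified by antihypertensive drug use at entry (yes/no), in permuted blocks of randomly varying size that are not disclosed to recruiters, with one series of sealed opaque envelopes per stratum. In section 9, state that the primary blood pressure model includes drug use at entry and baseline 24-hour blood pressure.

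The cost is a new list, a second envelope series and a sentence each in sections 4.1 and 9. The downside is slightly more predictable allocation in an open single-centre trial. If that is not acceptable, keep the simple list and add the two model terms alone. They recover most of the gain, at a variance cost of about 4% under a 20-point imbalance in drug use with half the patients on drugs. In either case, state whether the list is fixed at 28 per arm.

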### Estimation of sample size

4.2

The purpose of this study is to observe that the antihypertensive effect of acupuncture combined with medicine is not inferior to that of Western medicine alone. Therefore, the sample calculation is based on the sample content calculation formula of noninferiority test.^[8]^ The calculation result is 22.57, that is, the experimental group and the control group need about 23 patients, respectively. According to the shedding rate of 20%, a total of 56 patients will be recruited.

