## Statistical analysis

9

SPSS 20.0 statistical software will be used for data statistics (SPSS Inc, Chicago, IL). The frequency percentage will be used to describe the demographic data. For the measurement data with normal distribution and homogeneous variance, mean ± standard deviation (\bar{x} (Latex code) ± s) will used to describe the data. Paired and independent sample *t* test will used for intragroup and intergroup comparison respectively. For the measurement data of non-normal distribution, nonparametric test will be used. The blood pressure value will be analyzed by repeated measurement analysis of variance. In the correlation analysis of 2 theoretically related continuous variables, Pearson correlation coefficient model will be used if the data meet the normal distribution, and Spearman correlation coefficient model will be used if the data are nonnormal distribution. *χ*^2^ test will be used for counting data. All tests will be bilateral; *P* < .05 means the difference is statistically significant. In the correlation analysis, 0 < R≤0.2 means that there is no correlation between variables; 0.2<R≤0.4 means that there is a low correlation between variables; 0.4<R≤0.8 means that there is a moderate correlation between variables; 0.8 < R≤1 means that there is a high correlation between variables.

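### The trial is sized to show that medicine plus acupuncture is not inferior to medicine alone, which cannot answer its efficacy question and is not what the planned two-sided difference tests examine

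*Protocol article*

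**What the plan says.** **Sizing hypothesis.** Section 4.2 (Estimation of sample size) gives the purpose as observing that "the antihypertensive effect of acupuncture combined with medicine is not inferior to that of Western medicine alone", and for that reason "the sample calculation is based on the sample content calculation formula of noninferiority test". It continues: "The calculation result is 22.57, that is, the experimental group and the control group need about 23 patients, respectively". Then: "According to the shedding rate of 20%, a total of 56 patients will be recruited".

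**Design.** Section 2.1 has patients "divided into control group and experimental group according to the ratio of 1:1" and says of the two arms: "The latter will receive acupuncture treatment for 4 weeks on the basis of the former". Sections 5.1 and 5.2 confirm that both arms take western antihypertensive drugs on a cardiologist's advice. The control arm keeps its existing drugs, and only the experimental arm adds acupuncture.

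**Aim.** The Introduction says of acupuncture for hypertension: "Whether it can produce better therapeutic effect on hypertension is the focus of our research". Its closing paragraph gives the purpose as evaluating efficacy and safety. The Abstract expects favourable evidence of efficacy, and the Discussion says the design verifies the blood-pressure-lowering effect.

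**Analysis.** Section 9 lists paired and independent t tests, nonparametric alternatives and repeated-measures analysis of variance for blood pressure. It adds "All tests will be bilateral" and defines P < .05 as a statistically significant difference.

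**The concern.** Call the background drug A and acupuncture B. The comparison is A+B against A. The statement that A+B is not inferior to A is true whenever B does no material harm, including when B has no effect at all. Meeting that hypothesis therefore says nothing about whether acupuncture lowers blood pressure, which is the question the article sets out to answer.

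The sizing and the analysis also concern different hypotheses. The 22.57 comes from a formula for rejecting inferiority by some margin. Section 9 tests for a difference from zero. Power calculated for the first does not carry over to the second.

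What is at stake is the meaning of the primary result. Judged by section 4.2, a success would not be evidence of efficacy. Judged by section 9, the trial has no stated power for the test it performs.

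**Working it through.** **Inputs from the article:** 22.57, 23 per arm, 20% loss and 56 in total (section 4.2); 1:1 allocation (section 2.1); two-sided tests at 0.05 (section 9). The article gives no margin, SD, alpha, power or assumed difference with the formula. These may be in the full protocol and are not counted as an error. Results below are in SD units, over conventional choices of alpha and power that are my assumptions.

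**1. The plan's own figures.** 22.57 cannot be reproduced without those inputs. The total can: 23 × 1.2 = 27.6, rounded up to 28 per arm, or 56. A 20% loss from 56 leaves 56 × 0.8 / 2 = 22.4 per arm, just under 23. (Dividing instead, 23 / 0.8 = 28.75, gives 29 per arm, or 58.)

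**2. Margin implied by 22.57, if no true difference was assumed.** From n = 2[(z₁₋α + z_power) / (margin/SD)]², margin/SD = √(2/22.57) × (z₁₋α + z_power) = 0.2977 × (z₁₋α + z_power).

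| One-sided alpha | Power | Sum of z | Margin/SD |
|---|---|---|---|
| 0.05 | 80% | 1.645 + 0.842 = 2.486 | 0.74 |
| 0.025 | 80% | 1.960 + 0.842 = 2.802 | 0.83 |
| 0.05 | 90% | 1.645 + 1.282 = 2.926 | 0.87 |
| 0.025 | 90% | 1.960 + 1.282 = 3.242 | 0.96 |

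**3. Chance that inert acupuncture passes such a test.** With 23 per arm the standard error is √(2/23) = 0.2949 SD, and P(pass) = Φ(margin/0.2949 − z₁₋α).
- 80% power, one-sided 0.025: Φ(0.834/0.2949 − 1.960) = Φ(0.868) = 0.81. One-sided 0.05 gives the same to two decimals.
- 90% power, one-sided 0.025: Φ(0.965/0.2949 − 1.960) = Φ(1.312) = 0.91. One-sided 0.05 gives 0.90.

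If the formula had instead assumed a true benefit b, the same 22.57 implies a margin smaller by b:

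| Assumed benefit | Inert passes, 80% design | Inert passes, 90% design |
|---|---|---|
| 0 | 0.81 | 0.90 to 0.91 |
| 0.1 SD | 0.70 | 0.83 |
| 0.2 SD | 0.57 to 0.58 | 0.74 |
| 0.3 SD | 0.44 | 0.62 (0.61 at one-sided 0.05) |

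A two-sided superiority test at 0.05 would favour inert acupuncture 2.5% of the time.

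**4. What the size delivers for a two-sided difference test.** Independent-samples t test, alpha 0.05, noncentral t:

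| Evaluable per arm | Difference for 80% power | Power at 0.5 SD |
|---|---|---|
| 23 | 0.84 SD | 38% |
| 22.4 (after 20% loss from 56) | 0.86 SD | 37% |

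These describe a single comparison of two means. A repeated-measures analysis would shift them by an amount that depends on within-patient correlation, which the article does not give.

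**The case against.** **Non-inferiority is a stated purpose.** Section 4.2 does call it the purpose, so one cannot say the article never names it as an aim. This objection stands, and it fixes the charge: the article gives two purposes that cannot both be primary.

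**The inputs and a non-inferiority analysis may be in the full protocol or analysis plan.** Two-sided 5% testing does not by itself rule out reading non-inferiority from a 95% confidence interval. That is fair, so neither the missing inputs nor the missing margin rule is held against the plan. It does not rescue the design, because no choice of margin turns A+B against A into a test of whether B works.

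**Inert acupuncture would not in fact succeed 81% to 91% of the time.** A reader might infer from the working that the trial as planned will declare useless acupuncture a success with its planned power. The documents do not support that. It would require a non-inferiority test, which section 9 does not list, and a formula that assumed zero true difference, which section 4.2 does not say. Under the tests that are listed, the chance is about 2.5%. Nor does the text show that the authors would take a non-significant difference as proof of non-inferiority. The fix only guards against it.

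**Keeping 56 patients fits the target to the size.** This has some force. About 0.86 SD is a large difference, and by the normal approximation 0.5 SD would need 63 per arm for 80% power before dropout. Whether 0.86 SD is plausible for add-on acupuncture cannot be judged from the article. Stating it openly lets the sponsor and readers judge.

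**Conclusion.** The concern holds as a contradiction within the article. The objective and sample size in section 4.2 do not fit the add-on design (sections 2.1, 5.1 and 5.2), the efficacy aim (Abstract, Introduction and Discussion) or the two-sided difference tests (section 9). Non-inferiority of an add-on to its own background treatment cannot answer the efficacy question, and the power behind 22.57 does not apply to the planned tests. This follows from the stated text and does not depend on the margin, SD or power.

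The size of the problem is conditional. If a non-inferiority test were run, inert acupuncture would pass with probability 0.81 to 0.91 when zero difference was assumed, or 0.44 to 0.83 when a benefit of 0.1 to 0.3 SD was assumed. For superiority, 56 patients less 20% give 80% power only for about 0.86 SD. These figures assume normal outcomes with equal SDs and the conventional alpha and power values tabulated above.

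**What to change.** Amend section 4.2 as follows.
- State one primary hypothesis: superiority of acupuncture plus medicine over medicine alone in 24-hour ambulatory blood pressure, two-sided alpha 0.05, consistent with section 9.
- Keep 56 patients and replace the non-inferiority calculation by what that number provides: 80% power for about 0.86 SD with 22.4 evaluable per arm after 20% loss (0.84 SD with 23), and about 37% to 38% power for 0.5 SD.
- State that a non-significant difference will not be interpreted as non-inferiority.
- Quote a smaller detectable difference from baseline adjustment only if section 9 is also changed to a baseline-adjusted analysis, with the correlation labelled as an assumption.

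Cost: a protocol amendment and a registry update, with no extra patients. The published detectable effect becomes less favourable. If the sponsor finds 0.86 SD implausible, the honest alternatives are a larger trial or describing this one as preliminary.

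### Recruiting 56 patients does not leave the required 23 per arm at the plan's own 20% loss rate; the gap is small

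*Protocol article*

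**What the plan says.** All the relevant figures are printed in the protocol article. Section 4.2 (Estimation of sample size) says that "the sample calculation is based on the sample content calculation formula of noninferiority test". It gives the outcome as "The calculation result is 22.57" and reads this as meaning that "the experimental group and the control group need about 23 patients, respectively". It then makes the allowance for dropout: "According to the shedding rate of 20%, a total of 56 patients will be recruited". The Methods part of the abstract repeats the total ("we will recruit 56 hypertensive patients with hyperactivity of liver yang"). Section 2.1 (Experimental design) has patients "divided into control group and experimental group according to the ratio of 1:1", so the 56 correspond to 28 per arm.

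The article does not show the formula that leads from 23 per arm to 56. It also gives no power, alpha, noninferiority margin or standard deviation.

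**The concern.** An allowance for dropout exists so that the required number is still available once the expected loss has occurred. A loss rate applies to the patients recruited. The requirement must therefore be divided by the fraction retained (0.8), not multiplied by 1.2. Multiplying by one plus the rate always falls short, and here the total of 56 matches that calculation.

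What is at stake is the consistency of the sample-size statement. A requirement, a loss rate and a recruitment total are printed together, and the third does not follow from the first two. If losses reach the planned level, the trial ends with fewer evaluable patients than the plan says it needs.

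**Working it through.** **Inputs.** Evaluable patients per arm: 22.57 calculated, 23 rounded (section 4.2). Loss rate: 20% (section 4.2). Total recruited: 56 (section 4.2 and abstract). Allocation: 1:1 (section 2.1), so 28 per arm. Total requirement: 2 × 23 = 46 rounded, 2 × 22.57 = 45.14 unrounded.

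**Reproducing the plan's 56.** Two routes reach it:
- Requirement × (1 + rate): 46 × 1.2 = 55.2, rounded up to an even 56. Per arm, 23 × 1.2 = 27.6, rounded up to 28.
- Unrounded requirement / (1 − rate), then rounded down: 22.57 / 0.8 = 28.2, taken as 28 per arm, 56 in total.

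**What 56 leaves at 20% loss.** 56 × 0.8 = 44.8, or 28 × 0.8 = 22.4 per arm. This misses 23 per arm by 0.6 and 22.57 per arm by 0.17. In total the gap is 46 − 44.8 = 1.2 patients against the rounded requirement and 45.14 − 44.8 = 0.34 against the unrounded one.

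**What loss 56 can absorb.** Keeping 23 of 28 in each arm allows 5 losses per arm: 5 / 28 = 17.9%. A sixth loss leaves 22.

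**Total needed at 20% loss, requirement / (1 − rate):**

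| Starting point | Calculation | Result |
|---|---|---|
| 46 in total | 46 / 0.8 = 57.5 | 58 |
| 23 per arm | 23 / 0.8 = 28.75 | 29 per arm, 58 |
| 22.57 per arm | 22.57 / 0.8 = 28.2 | 29 per arm, 58 |
| 45.14 in total | 45.14 / 0.8 = 56.4 | 57 (not divisible into equal arms) |

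Even the most lenient starting point gives more than 56.

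**Check of 58.** 58 × 0.8 = 46.4, or 23.2 per arm, which meets 23.

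**The case against.** Four things can be said for the plan.

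- **The target is approximate.** Section 4.2 says about 23. This does not close the gap, because 22.4 is also below the unrounded 22.57.
- **The 20% may be meant as a simple add-on.** Read as 20% of the number required, it gives 9.2 extra patients on 46, and 56 covers that. But the article calls it a rate of shedding, and a rate of loss is a share of those recruited. On that ordinary reading the figure fails.
- **Not every dropout leaves the analysis.** Section 3.5.2 mentions an intention analysis and keeps patients with more than half of the treatment course in the efficacy analysis. The number analysed could therefore exceed 44.8. This limits the practical harm but does not correct the calculation.
- **The cause is not documented.** Multiplication by 1.2 fits well, but so does correct division followed by rounding down. This objection stands, so the cause can only be called apparent. The shortfall is the same by either route.

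A reader might also infer that the trial misses its stated power, or might translate the gap into a larger detectable difference. The documents do not support this. No power is stated, and any such figure would need an assumed power, alpha, margin and standard deviation. Using a superiority test for it would also depart from the noninferiority basis given in section 4.2.

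**Conclusion.** The point holds as a minor arithmetic inconsistency. At the plan's own 20% loss, 56 recruited patients leave 22.4 per arm, short of the 23 required and of the calculated 22.57. The shortfall is 1.2 evaluable patients in total against the rounded requirement, and the properly inflated total is two patients higher. The conclusion assumes equal arms of 28 and a loss rate that applies to those recruited and removes them from the evaluable set. It does not depend on how 56 was reached or on how 22.57 was obtained; the latter cannot be checked from the article. Nothing in the design or the analysis changes because of it.

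**What to change.** Revise the last sentence of section 4.2 in one of two ways.

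- Keep 56 and state what it delivers: 28 per arm retain 23 if losses do not exceed 17.9% (5 of 28), or about 22 per arm remain at 20% loss. This costs one sentence and no patients.
- State 58 (29 per arm), which leaves 23.2 per arm at 20% loss. This costs two more patients, and the total in the abstract must change as well.

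Either way, show the inflation formula. Do not attach a power or detectable-difference figure to the correction unless the inputs behind 22.57 are reported with it.
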